### Intervention implementation

The intervention will be delivered over a period of 2–6 months in each of the settings. The follow-up visits will take place at the same school or community setting as the initial check-up. In addition to covering all clinical costs, the equivalent of US$5 will be given to each participant who attends the follow-up to cover any transport costs that they might have incurred. Additionally, health and hygiene related items will also be provided for adolescents to take home, including tooth cleaning kit (toothbrush and toothpaste), fruit, bottle of water, two pairs of underpants and pack of reusable sanitary pads (girls only).

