### Inclusion and exclusion criteria

To be included in the study, adolescents aged 10–19 years must fall into one of the first three categories below and fulfil category 4.

Be attending selected classes of year 5 of primary school in Mwanza (median age 11 years); grade 5/6 of primary school in Chitungwiza (median age 11 years) or year 1 of Junior Secondary School in Cape Coast (median age 12 years) ORBe attending selected classes in year 3 of Secondary School in Mwanza (median age 17 years), Form 3/4 in Chitungwiza (median age 17 years) or year 2 of Senior Secondary School in Cape Coast (median age 16 years) ORBe resident in a selected community during the time of the Y-Check intervention, and be aged 16–19 years

AND

Have a completed and signed Informed Consent form, or a signed Informed Assent Form and signed Parental/Guardian Informed Consent Form if the adolescent is seen in the community and is below the national age of consent or is seen in a school, irrespective of their age.

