### Data collection

#### During the Y-Check intervention and follow-up

Data collection during baseline and follow-up visits will include self-completed evaluation questionnaires, self-reported screening tool responses and screening visit consultations, measurements and specimen collection and an exit interview. Data on the implementation process and on adolescent outcomes will be collected in digital and paper-based formats. A user-friendly digital data collection app for the check-ups will be developed and housed on a tablet computer for direct use by the adolescent. Initial sections will include audio-assisted, user-friendly self-completion questions for adolescents to fill out. This will utilise engaging content and processes, tailored to adolescents’ interests. The option of a face-to-face interview will also be available if the adolescent is unable to use the tablet or has low literacy level. Health services registers and school registers will also be reviewed to determine the number of adolescents of the relevant age ranges, and school attendance by the classes involved in Y-Check. To help build the referral process, existing adolescent services will be mapped in the study communities.

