### Study outcomes

Outcomes will be ascertained during the check-up screening visit and through collection of referral vouchers from the referral health facilities, and, for outcomes related to health and well-being impacts, through data from the 4 month and, in Zimbabwe only, 12 month follow-up visits. Outcomes related to completed referrals will be triangulated against participants’ self-reports at the 4 month and in Zimbabwe only, 12 month follow-up visits. Review of school and health service registers will be used to see whether attendance has increased during the period when Y-Check is being implemented.

The primary outcome will be the proportion of those screening positive for at least one condition who receive appropriate on-the-spot care or complete appropriate referral for all identified conditions within 4 months. This will be measured using data collected at the initial check-up visit and through recovery of referral vouchers given to participants to allow them to access referral services for free during the 4 months after the Y-Check screening. Completed referral is defined as attending at least the first referral appointment.

Secondary implementation outcomes will include the proportion of those screening positive for each condition who receive appropriate on-the-spot care or complete appropriate referral for that condition within 4 months, the yield of previously untreated conditions, clinical outcomes at 4 months among those who had originally screened positive for each condition, and intervention acceptability, adoption, appropriateness, feasibility, fidelity and cost. Secondary effectiveness outcomes will include knowledge about health services and health behaviours, self-reported agency and self-efficacy to make decisions about their health, self-reported health-related risk and protective behaviours, reported engagement with health services, well-being, self-esteem and quality of life, clinical outcomes and educational outcomes, which will be collected within the Y-Check and follow-up visits. The short-term cost-effectiveness of the intervention will be estimated (calculated by a comparison of the costs of the intervention against the primary and secondary outcomes and including short-term changes in self-reported quality of life). All outcomes for the study are described in table 3.

**Table 3 T3:** Study outcomes and means of verification

Outcome	Sources of data

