**Client outcomes**	
Knowledge about health services and health behaviours.	Programme monitoring data including records of attendance for referrals. Screening tool (self-reported symptoms or conditions, measurements and clinical actions). Self-completed evaluation questionnaire.
Intentions to adopt healthy behaviours.	
Agency to make decisions about health and well-being.	
Perceived social support for behaviour change.	
Health-related risk and protective behaviours.	
Improvement in previously diagnosed health and well-being conditions.	
Engagement with health and other services within the past 4 months.	
Self-esteem.	
Self-perceived well-being.	
Quality of life.	
Clinical outcomes.	
Educational outcomes (eg, school attendance).	Self-completed evaluation questionnaire. School register review.
Client-defined outcomes (to be determined).	Self-completed evaluation questionnaire. Exit interviews.

DALYs, Disability Adjusted Life Years; QALYs, Quality Adjusted Life Years.

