Secondary outcomes which are measured at a single-time point will be presented in a similar way to the primary outcome. For outcomes which are measured at two or more time points, a before–after analysis will be conducted comparing differences in measures between the time points. The unit of analysis will be the individual. For clinical outcomes which are measured at two or more time-points, the initial check-up visit (baseline) will give the prevalence of untreated conditions which will represent the counterfactual. The prevalence of conditions at the 4 month follow-up visit will be formally compared with this counterfactual to estimate the short-term effects of the intervention in improving these clinical outcomes. For analysis of outcomes measured at two timepoints, we will use mixed-effects logistic regression (binary outcomes) or linear regression (continuous outcomes) adjusting for individual-level clustering as a random effect and school/community as a fixed effect. Health service and client determinants of correct management of conditions at 4 months will be analysed using multivariable regression.

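### School attendance is measured by a questionnaire given at the school and by a register read by class, so school-recruited adolescents who stop attending are likely to be under-represented in an individual before–after analysis

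*Protocol article*

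**What the plan says.** All references are to the protocol article.

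- **Outcome.** Study outcomes lists, among the secondary effectiveness outcomes, "well-being, self-esteem and quality of life, clinical outcomes and educational outcomes, which will be collected within the Y-Check and follow-up visits". Table 3, Client outcomes, names the example: "Educational outcomes (eg, school attendance".
- **Sources.** Table 3 gives two for this outcome: "Self-completed evaluation questionnaire. School register review".
- **Entry.** Inclusion and exclusion criteria admits school participants through class attendance, for example "Be attending selected classes of year 5 of primary school in Mwanza". A separate stratum is recruited in the community at ages 16–19.
- **Place of follow-up.** Intervention implementation says: "The follow-up visits will take place at the same school or community setting as the initial check-up". Each participant who attends receives the equivalent of US$5 for transport.
- **Register.** Data collection describes the register review as covering "school attendance by the classes involved in Y-Check". Study outcomes gives its purpose: "Review of school and health service registers will be used to see whether attendance has increased during the period when Y-Check is being implemented".
- **Analysis.** Statistical analysis says "The unit of analysis will be the individual". It compares time points with mixed-effects logistic or linear regression, with a random effect for the individual and school or community as a fixed effect. Baseline is the counterfactual, and there is no concurrent comparison group.

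**The concern.** For a school-recruited participant, the place where attendance is asked about is the place whose attendance is in question. A learner who has dropped out, changed school or is often away is less likely to be present on the follow-up day. Whether the outcome is observed then depends partly on the outcome itself.

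Selection at entry adds to this. Everyone in the school stratum is attending a selected class at baseline, so enrolment status can only stay the same or worsen, and those for whom it worsens are the easiest to miss.

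The register could fill the gap because it does not depend on who comes to the visit. As described, though, it is read by class. A class is not the cohort: it includes classmates outside the study and later joiners, and it may drop leavers. A class-level figure also cannot enter a model of individuals. The window given for it is the implementation period, not each participant's own months before and after the check-up.

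With no comparison group, selective loss goes straight into the before–after estimate. At stake is the sign of the reported change in one secondary outcome.

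**Working it through.** **The plan's own figure.** The article gives no attendance rate, school-leaving rate or expected loss to follow-up. Its one precision figure, ±7% under Sample size, concerns the primary outcome. It reproduces, 1.96 × √(0.75 × 0.25 / 150) = 0.069, and has no bearing here.

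**Case 1: attendance falls after baseline.** Assumptions, none from the documents: stayers attend 92% of days in both periods; leavers attend 60% before and 0% after; a share *d* leaves; no leaver is seen at follow-up.

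- Baseline mean, all enrolled: (1 − d) × 92 + d × 60
- True follow-up mean, all enrolled: (1 − d) × 92 + d × 0
- Follow-up mean among those seen: 92

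| d | Baseline, all | True follow-up | True change | Unpaired change, available records | Change among completers |
|---|---|---|---|---|---|
| 2% | 91.36 | 90.16 | −1.2 | +0.6 | 0 |
| 5% | 90.40 | 87.40 | −3.0 | +1.6 | 0 |
| 10% | 88.80 | 82.80 | −6.0 | +3.2 | 0 |

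If leavers instead stay on the roll, are marked absent and are read individually, the register returns the true change.

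**Does the planned model repair Case 1?** Take a random-intercept linear model with two time points and some follow-up values missing. For a given within-person correlation ρ, the estimated follow-up mean is

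mean at follow-up of those seen + ρ × (baseline mean of all − baseline mean of those seen).

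For d = 5% this is 92 + ρ × (90.4 − 92). The estimated change is 92 − 1.6ρ − 90.4 = 1.6 × (1 − ρ), which lies between 0 and +1.6 for ρ between 0 and 1. The true value is −3.0. The model cannot reach it, because no record of the fall is in the data.

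**Case 2: stable low attenders.** Assume 10% attend 50% of days and 90% attend 95%, unchanged over time, with half of the low attenders missed at follow-up.

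- True mean at both times: 0.9 × 95 + 0.1 × 50 = 90.5
- Mean among those seen at follow-up: (0.9 × 95 + 0.05 × 50) / 0.95 = 92.6
- Unpaired difference: 92.6 − 90.5 = +2.1, against a true change of 0

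By the same formula the model gives 2.1 × (1 − ρ). When low attendance is a stable trait, ρ is close to 1. In a simulation of this case (2000 pupils, 60 school days per period assumed) the random-intercept model gave about +0.1. The planned model therefore largely removes this bias.

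**The case against.** **Leavers can be counted.** A reader might infer that adolescents who stop attending cannot be counted at all. The documents do not support that. The article fixes a venue, not a condition of continued enrolment, and the transport payment goes to anyone who attends. A former learner may come, a register shows absence while the name stays on the roll, and community recruits are followed at community venues. This stands: under-represented is the supportable claim.

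**The register may be read individually.** Describing attendance by class does not exclude reading named entries, and class totals would suit the stated use of seeing whether attendance rose. This stands in part. On either reading, the article does not tie the register to the participants whose change is to be modelled.

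**The model deals with it.** For stable low attenders it largely does, so the 2-point gain in Case 2 should not be claimed against the planned analysis. For a fall after baseline it does not.

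**The direction is not certain.** Among completers the result is a missed fall, not a false rise. Selecting learners who are attending could also pull later attendance down through regression to the mean. This stands: upward is the likely direction, not one fixed by the design.

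**Tracing and linkage may be in the full protocol.** They may be, and their absence from an article is no fault. The point rests on the venue, the class-level description and the individual unit of analysis, all of which are stated.

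**Conclusion.** The point holds for school-recruited participants and for school attendance. The two stated sources are likely to under-represent those who stop attending after baseline, and the planned mixed model does not correct for that. A fall would be hidden or, in an unpaired comparison, could appear as a rise.

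The size is unknown. The illustrative range for 2% to 10% leaving is a true change of −1.2 to −6.0 points, against 0 among completers and +0.6 to +3.2 in available records. This rests on the assumed attendance rates and on no leaver being seen. Any leavers who return for the visit shrink the gap. Table 2 gives lower net enrolment in secondary than in primary school in all three settings (86% and 57%, 82% and 39%, 94% and 54%). These figures make school leaving plausible, but they are not 4-month leaving rates and cannot size the effect.

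A reader might extend the point to the clinical and behavioural outcomes, or expect greater loss at Zimbabwe's 12-month visit. The documents give no figures for either, so neither is claimed. The primary outcome is unaffected: Sample size says it does not require the 4-month follow-up data.

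This is worth changing because the sign of a named secondary effectiveness outcome may be wrong and the remedy is cheap. It does not threaten the study's main result.

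**What to change.** 1. Make the baseline list of school-recruited participants the denominator for school attendance.
2. Take each participant's own register entries over equal periods before and after that participant's check-up, whether or not they are seen at follow-up.
3. Count confirmed dropouts as not attending. Report transfers and unknown status separately, with a sensitivity analysis over how they are scored. Scoring everyone who leaves the register as not attending would misclassify those who moved school.
4. Treat the questionnaire item as supportive.
5. Under Intervention implementation, allow school-recruited participants who no longer attend to have their follow-up at an existing community venue, with the same transport payment.

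The registers are already to be reviewed and the community venues already exist. The cost is the time to extract named entries and some contact attempts. If follow-up visits are already complete, item 5 no longer applies, but the register extraction may still be possible retrospectively.

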### Composition and training of Y-Check team

The Y-Check team will be trained to deliver adolescent-responsive and age-appropriate services according to national and WHO guidelines, recognising also the needs for privacy and confidentiality.^28^ This includes providing services that are attractive to adolescents, meet their needs comfortably and responsively and that are attentive to their privacy. These principles and approaches will be embedded into each part of the Y-Check intervention. Visual and auditory privacy will be prioritised, through the use of separate tents, rooms or screens. Health workers will employ standard gowning and draping for clinical procedures.

For infection prevention and control, all study procedures including interviews, physical examinations and blood tests will take place in well-aerated tents or outdoors, and will follow relevant nationally approved protocols for all staff and participants.

The Y-Check team will be trained in good clinical practice, data protection and confidentiality and clinical staff will be trained in counselling for participants testing positive for any of the conditions being screened for within Y-Check as well as in general counselling skills.

### Inclusion and exclusion criteria

To be included in the study, adolescents aged 10–19 years must fall into one of the first three categories below and fulfil category 4.

Be attending selected classes of year 5 of primary school in Mwanza (median age 11 years); grade 5/6 of primary school in Chitungwiza (median age 11 years) or year 1 of Junior Secondary School in Cape Coast (median age 12 years) ORBe attending selected classes in year 3 of Secondary School in Mwanza (median age 17 years), Form 3/4 in Chitungwiza (median age 17 years) or year 2 of Senior Secondary School in Cape Coast (median age 16 years) ORBe resident in a selected community during the time of the Y-Check intervention, and be aged 16–19 years

AND

Have a completed and signed Informed Consent form, or a signed Informed Assent Form and signed Parental/Guardian Informed Consent Form if the adolescent is seen in the community and is below the national age of consent or is seen in a school, irrespective of their age.

### Consent and assent procedures

Before the visit of the implementation team, information on the Y-Check programme will be distributed to parents/guardians through the schools and to community members through an active communication campaign in collaboration with the CAC and the YAG. School and community meetings will allow parents and community members to ask questions about the programme and give their feedback.

In schools, adolescents will have a short introductory meeting with a member of the Y-Check team typically in a class or group setting. Parent meetings will then be held in each of the schools, to which all the parents and guardians of eligible learners will be invited. During these sessions, information will be provided about the study, its objectives and procedures, possible risks and procedures that will be used to maintain confidentiality. These meetings will provide an opportunity for the adolescents, parents and guardians of eligible adolescents to learn more about the Y-Check intervention and the research linked to it and to have their questions answered.

No participants will be screened, receive care or be counselled or interviewed without their informed consent (community participants who are above the national age of consent), or, for minors, their assent and parental consent, unless they are determined to be emancipated minors.^29^ Following advice from Ministries of Education in all three countries, all adolescents seen in schools will be considered to be minors and require parental consent, irrespective of their age.

Minor adolescents’ assent will be ascertained and documented in an assent form. Parents or guardians who would like their adolescent to receive the check-up will be asked to provide their written consent. On the day of the check-up visit, a verbal confirmation of their previous written assent will be requested from the adolescent. In Ghana and Tanzania, where the minimum age for providing consent to medical and health-related research is 18 years, clients of all ages under 18 will provide completed parental consent forms and provide written assent before proceeding through the check-up visit regardless of whether the check-up is in schools or communities. In Zimbabwe, a waiver of parental consent has been given by the Medical Research Council of Zimbabwe (MRC-Zimbabwe) so that participants aged 16 and 17 years who attend the check-ups in the community venues will be allowed to provide written consent for themselves.

The intervention will be conducted in private and not in the presence of the parent or guardian. Contact details of the study team will be shared with participants in case they have questions at a later stage. All participants will be reminded that participation is entirely voluntary and will be told that they can opt out of the research or services at any time.

### Data collection

#### During the Y-Check intervention and follow-up

Data collection during baseline and follow-up visits will include self-completed evaluation questionnaires, self-reported screening tool responses and screening visit consultations, measurements and specimen collection and an exit interview. Data on the implementation process and on adolescent outcomes will be collected in digital and paper-based formats. A user-friendly digital data collection app for the check-ups will be developed and housed on a tablet computer for direct use by the adolescent. Initial sections will include audio-assisted, user-friendly self-completion questions for adolescents to fill out. This will utilise engaging content and processes, tailored to adolescents’ interests. The option of a face-to-face interview will also be available if the adolescent is unable to use the tablet or has low literacy level. Health services registers and school registers will also be reviewed to determine the number of adolescents of the relevant age ranges, and school attendance by the classes involved in Y-Check. To help build the referral process, existing adolescent services will be mapped in the study communities.

#### Process evaluation

The process evaluation is guided by the UK MRC’s Process Evaluation framework to understand intervention implementation (including feasibility and fidelity), mechanisms of impact (including acceptability and uptake) and the influence of context.^30^ Key implementation outcomes of interest are acceptability, adoption, appropriateness, feasibility and fidelity. Data on contextual factors and barriers and facilitators to programme implementation will be gathered using routinely collected programme monitoring data. Qualitative data will be collected through (1) observations of the Y-Check intervention and referrals, as well as team meetings; (2) in-depth interviews with eligible adolescents who received, adolescents who were referred and adolescents who did not receive Y-Check, as well as with school authorities and the Y-Check service providers and (3) participatory workshops with teachers, adolescents and parents. Quantitative programme monitoring data will be collected routinely within the Y-Check visit, including through a participant exit interview. Process evaluation data will be analysed iteratively and thematically, through regular analytical discussions and analytical memos to draw out the main themes emerging from the data. Across the pilot and intervention studies, data collection for the process evaluation will include real-time feedback to the implementation team.

